| **Diagnosis and Main Criteria for Inclusion/Exclusion:**  **Main Inclusion:**   - Newly diagnosed, histologically confirmed the following pathology subtype according to WHO 2008   classification: Follicular Lymphoma I-IIIA.   - ≥ 16 years of age. - Performance status of 2 or less. - Has no history of malignancy. - Has radiologically measurable disease. - Life expectancy ≥3months. - Voluntarily sign an informed consent. | |
| **Diagnosis and Main Criteria for Inclusion/Exclusion (Continued):**  **Main Exclusion:**   - Previous systemic chemotherapy or local therapy. - Has undergone hematopoietic stem-cell transplantation (HSCT). - Has previous treatment of lenalidomide. - Has an active infectious disease requiring general antibiotics, antifungal, or antiviral therapy. - Has an uncontrollable medical condition that might interfere with their participation in the study. - Echocardiography shows left ventricular ejection fraction (LVEF) ≤ 50%. - Woman in pregnancy or lactation. - Patient is known to be positive for Human immunodeficiency virus (HIV) infection. | |
| **Treatment** | |
| Study Group | Interventions |
| Rituximab plus lenalidomide Group | R2 (at each cycle):  Rituximab 375mg/m^2^, intravenously, Day 0  Lenalidomide 25mg, orally, Day 1-10  Every 21 days for 6 cycles |
| **Duration of Treatment:** A total of 6 cycles of treatment. | |
| **Criteria for Evaluation:**  **Efficacy:**  Positron emission tomography-computed tomography (PET-CT) will be evaluated at baseline, after three cycles for interim evaluation and at EOT for final evaluation. | |
| **Criteria for Evaluation (Continued):**  Responses will be assessed according to 2014 Lugano criteria for non-Hodgkin lymphoma. Central response assessment of PET and CT images will be performed by radiologists of Shanghai Ruijin Hospital, who are not informative of the treatment group. CT scans of the neck, thorax, abdomen, and pelvis will be repeated every three months thereafter to monitor disease progression in the first year, then every six months in the following two years, and yearly thereafter.  **Safety:**  The severity of adverse events will be assessed according to the CTCAE v4.0. | |

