| **Statistical Plans:**  Statistical analysis will be conducted by or under the supervision of the study statistician. Statistical analysis will be performed using SPSS and GraphPad Prism.  The statistical analysis sets are defined as follows: The intention-to-treatment population (ITT) is defined as all subjects who were randomized to either of the treatment group and accepted at least one dose of treatment. ITT sets can be used for efficacy/safety analysis and demographic/baseline characteristics analysis.  The Fisher's exact test will be applied to categorical variables as appropriate. Analysis of covariance, or rank-sum test will be used, as appropriate, for continuous variables. Survival estimates will be calculated using Kaplan-Meier method. Log-rank test will be used to compare survival time between treatment groups. Univariate hazard estimates were generated with the Cox regression methods. Cox regression additionally required that the hazard ratio be proportional, which was calculated by Schoenfeld residual test. If the P value was ≥ 0.05, then the hazard ratio was considered proportional. Thereafter, variables with P value < 0.05 in univariate analyses were included in the multivariable sets.  The primary endpoint will be CRR at the end of treatment. Secondary endpoints will include ORR, PFS, OS and adverse events.  **Variable definition:**  Complete Response Rate (CRR): CRR was assessed by the investigators according to the Lugano 2014 criteria.  Objective response rate (ORR): ORR was defined as the proportion of patients with a complete response or partial response to treatment according to Lugano 2014 criteria.  Progression-Free Survival (PFS): PFS was defined as start date of treatment and ended with the date of disease progression or the last follow-up.  Overall Survival (OS): OS was recognized from start date of diagnosis and ended with the date of death or the last follow-up.  **Assumptions:**  We estimate that 73% of patients in the R2 group would achieve CR. One-hundred and fifty patients will be required to show this difference with 5% significance (two-sided) and 90% power. The number of patients achieving CR at the end of study will be reported by treatment group with 95% CI using normal approximation. Sample size was calculated by PASS software (NCSS, Kaysville, UT).  **Data quality assurance:**  To ensure good quality data, investigators and study site personnel will be familiarized with the study protocol, study procedures and principles of GCP during the trial initiation visit. All the data will be placed into the local database via a data registry server managed by the data collection group.  All adverse clinical experiences, whether observed by the investigator or reported by the patient, will be recorded, with details about the duration and intensity of each episode, the action taken with respect to the test drug, and the patient’s outcome. The investigator will evaluate each adverse experience for its relationship to the test drug and for its seriousness. CTCAE term (AE description) and grade: The descriptions and grading scales found in the revised NCI Common Terminology Criteria for the CTCAE v4.0. will be utilized for AE reporting. Concomitant medications will be coded using WHO Drug Reference List.  **Handling of missing data:**  Every effort will be made to contact patients who fail to return for scheduled visits. A patient is considered lost to follow-up if no information has been obtained by investigator for one year and at least three unsuccessful documented attempts of contact are available in source documentation. Missing or incomplete data for survival are managed by censored data analyses.  **Follow-up plan:**  Follow-up period will start at the end of treatment or at treatment discontinuation. Patient will be followed every 3 months for the first year and every 6 months up to end of follow-up period.  Follow-up assessments include:  • Physical examination including ECOG PS  • Hematology laboratory evaluations (RBC count, hemoglobin, hematocrit, WBC count and ANC, and platelet count)  • CT scans every 3 months for the first year and every 6 months for the second year and then every year until disease progression/relapse or end of follow-up period. | |

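### OS is timed from diagnosis although only treated patients are analysed, so survival guaranteed before the first dose is counted and OS is biased upward, probably by a small amount

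*Protocol*

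**What the plan says.** All of the relevant text is in the Protocol synopsis.

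- **OS origin** (Statistical Plans, Variable definition): "OS was recognized from start date of diagnosis and ended with the date of death or the last follow-up".
- **PFS origin** (same place): "PFS was defined as start date of treatment and ended with the date of disease progression or the last follow-up".
- **Analysis set** (Statistical Plans): membership requires that the patient "accepted at least one dose of treatment". This set serves the efficacy analyses.
- **Estimator** (Statistical Plans): "Survival estimates will be calculated using Kaplan-Meier method". Delayed entry and left truncation are not mentioned.
- **Eligibility** (Main Inclusion and Main Exclusion): "Newly diagnosed, histologically confirmed the following pathology subtype according to WHO 2008", with "Previous systemic chemotherapy or local therapy" as an exclusion. No maximum time from diagnosis to first dose is listed.
- **Role of OS** (Statistical Plans): "Secondary endpoints will include ORR, PFS, OS and adverse events".

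No reason is given for using different origins for OS and PFS.

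**The concern.** A patient enters the analysis only by living long enough to receive a first dose. A patient who died after diagnosis but before treatment is not in the data. If the OS clock starts at diagnosis and the estimator is ordinary Kaplan-Meier, every analysed patient contributes a stretch of follow-up in which death was impossible. This is immortal time. It lifts the curve by an amount set by the delay before treatment, which says nothing about the regimen.

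The trial has one arm, so no concurrent control shares the bias. Anyone who sets the reported OS beside outside data timed from treatment start would carry the whole shift into that comparison.

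A smaller consequence is that OS and PFS at the same nominal time refer to different moments in a patient's course, offset by the gap.

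**Working it through.** The protocol gives no OS rate, OS event count or OS power, so there is no stated OS figure to reproduce. The check has two parts.

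**1. Direction, without a model.** Let patient *i* have gap *gᵢ* ≥ 0 from diagnosis to first dose, and survive *Tᵢ* after first dose. Measured from diagnosis, survival is *Tᵢ + gᵢ*. With follow-up complete to time *t*, the proportion with *Tᵢ + gᵢ > t* can never be lower than the proportion with *Tᵢ > t*. It is higher whenever a death falls in the shifted window. No assumption about the shape of the hazard is needed.

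**2. Size, under stated assumptions.**

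Inputs:
- Origin, analysis set and estimator: from the Protocol, as above.
- Gap *g*: not stated. Assumed common to all patients, 0.5 to 12 months.
- True 36-month OS from first dose: not stated. Assumed 90%, with 80% and 95% as a range.
- Constant hazard after first dose: assumed.

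Formulas:
- Monthly hazard: *h* = −ln(S₃₆)/36. For 90%, *h* = 0.10536/36 = 0.002927.
- OS as reported at 36 months from diagnosis: exp(−*h*(36 − *g*)).

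For example, with *g* = 1 the result is exp(−0.002927 × 35) = 0.9026, and with *g* = 3 it is exp(−0.002927 × 33) = 0.9079.

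| Gap, all patients (months) | Reported OS if true 90% | Excess, true 90% (points) | Excess, true 95% | Excess, true 80% |
|---|---|---|---|---|
| 0.5 | 90.1% | +0.1 | +0.07 | +0.25 |
| 1 | 90.3% | +0.3 | +0.1 | +0.5 |
| 3 | 90.8% | +0.8 | +0.4 | +1.5 |
| 6 | 91.6% | +1.6 | +0.8 | +3.0 |
| 12 | 93.2% | +3.2 | +1.6 | +6.2 |

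**Mixed gaps.** Suppose 85% of patients start after 1 month and 15% after 24 months, again with a true 90%. Then 0.85 × exp(−0.002927 × 35) + 0.15 × exp(−0.002927 × 12) = 0.85 × 0.9026 + 0.15 × 0.9655 = 0.912. That is about +1.2 points.

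**Scale.** For a 36-month OS of 90% with complete follow-up, the standard error with 115 patients is √(0.9 × 0.1/115) = 2.8 points, so the 95% half-width is about 5.5 points. With 150 patients, the other number in the synopsis, the half-width is about 4.8 points.

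**The case against.** The strongest reply is that the effect is too small to matter. Entry is limited to newly diagnosed, previously untreated patients, which is a qualitative limit on the gap even without a number. Nothing in the protocol describes a planned observation period before treatment. At a gap of a few weeks the shift is a small fraction of the sampling error. OS is secondary, with no hypothesis, threshold or power attached, and a single-arm trial has no treatment contrast to distort.

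Most of this stands, and it limits the size of the point. It does not remove the point: sampling error does not excuse a bias of known direction, and the listed criteria do not rule out an untreated interval after diagnosis.

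Three stronger readings are tempting but not supported:

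- **That OS is grossly exaggerated.** In the 12-month row, 3-year mortality reads 6.8% instead of 10%, about 32% lower in relative terms. That requires every patient to wait a year, and nothing in the protocol suggests this.
- **That the Cox results for OS are biased.** This would require the gap to be related to a covariate in the model. The protocol gives no evidence of such a relation and does not say which endpoint the Cox models serve.
- **That the OS and PFS curves cannot be read together.** They are offset by the gap. If that is a matter of weeks, this is an inconsistency to tidy, and the curves remain usable.

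**Conclusion.** The point holds in a limited form. Timing OS from diagnosis in a set restricted to treated patients, with ordinary Kaplan-Meier, biases OS upward. That follows from the protocol's own definitions and needs no outside figure.

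The size cannot be fixed from the document, because both the gap and the true OS are assumptions. With a true 3-year OS of 90%, a constant hazard and a common gap, 0.3 to 0.8 points (gaps of 1 to 3 months) is the range to have in mind. The 6- and 12-month rows show an extreme and are not an estimate for this trial. The primary endpoint is untouched, and no decision rule in the protocol depends on OS. The change is worth making because it costs almost nothing and removes a bias whose direction is known and whose size is uncontrolled.

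**What to change.** Reword the OS definition so that it runs from the date of first dose, the same origin as PFS, to death, with censoring at last follow-up. The event and censoring rules stay as they are. This measures survival from the start of the regimen, which is what the trial sets out to evaluate.

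If survival from diagnosis is wanted, keep that origin but left-truncate at first dose, so that each patient joins the risk set only on the day treatment starts.

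The cost is one sentence. The endpoint definitions already require both dates, so no new data are needed, and no clinical procedure changes. Reported OS will be slightly less favourable.

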**Study Protocol**

**Protocol title:** A Phase 2, single-arm, phase 2 trial of rituximab plus lenalidomide in FL.

| Protocol number | NHL-R2 |
| --- | --- |
| Date: | 01 Sep, 2018 |
| Study Phase: | 2 |
| Study Design: | This is a phase 2 trial to evaluate the efficacy and safety of rituximab plus lenalidomide in patients with newly diagnosed FL. |
|  |  |

| **Synopsis** | |
| --- | --- |
| **Protocol Number:** NHL-R2 | **Study phase:** 2 |
| **Date of Protocol Synopsis:** 01 SEP, 2018 | |
| **Protocol Title:** A Phase 2, single-arm, phase 2 trial of rituximab plus lenalidomide in FL. | |
| **Objectives:**  **Primary objective:** The primary objective is to evaluate the complete response rate (CRR) at the end of treatment of rituximab plus lenalidomide in patients with newly diagnosed follicular lymphoma (FL).  **Secondary objectives:** The secondary objectives are to evaluate the complete response rate (ORR), progression free survival (PFS) and overall survival (OS). The safety will also be evaluated by number of participants with treatment-related adverse events as assessed by the Common Terminology Criteria for Adverse Events (CTCAE) version 4.0. | |
| **Study Sites:** Shanghai Rui Jin Hospital | |
| **Study Population:** Newly diagnosed patients with FL | |
| **Number of Subjects to be Enrolled:** 115 patients | |
| **Background:**  Non-Hodgkin lymphoma (NHL) is the indolent tumor originated in lymph nodes and other lymphoid tissues and the incidence is growing up at 3%-4% per year. Follicular lymphoma (FL) is a heterogeneous entity of non-Hodgkin lymphoma (NHL), accounting for 10%-20% of NHL. Rituximab, cyclophosphamide, doxorubicin, vincristine, and prednisolone (RCHOP) or RCHOP-like chemotherapy is widely used in FL. However, rituximab plus chemotherapy has considerable side effects, particularly hematological toxicity and non-hematological immunosuppression, gastrointestinal and cardiac events. Multiply combinational regimens have been attempted in FL, rituximab plus immunomodulatory agent lenalidomide (R2) achieve similar clinical efficacy as rituximab plus chemotherapy in newly diagnosed FL with less chemotherapy-associated side effects. We plan a phase 2, single-arm trial to evaluate the efficacy and safety of rituximab plus lenalidomide in a Chinese cohort of newly diagnosed patients with FL. | |

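### The sample-size paragraph claims 90% power for a difference, but this single-arm plan gives one rate, no reference CRR and no test, so the claim belongs to no planned analysis

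*Protocol*

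**What the plan says.** The synopsis describes a trial with one arm: "We plan a phase 2, single-arm trial to evaluate the efficacy and safety of rituximab plus lenalidomide". Its aim is stated without a comparison: "The primary objective is to evaluate the complete response rate (CRR) at the end of treatment of rituximab plus lenalidomide".

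Under Statistical Plans, the Assumptions paragraph gives an expected rate, "We estimate that 73% of patients in the R2 group would achieve CR", and continues: "One-hundred and fifty patients will be required to show this difference with 5% significance (two-sided) and 90% power". It then sets out how the primary endpoint will be presented: "The number of patients achieving CR at the end of study will be reported by treatment group with 95% CI using normal approximation".

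The only test named for categorical data is general: "The Fisher's exact test will be applied to categorical variables as appropriate". The Background says that the combination performs similarly to rituximab plus chemotherapy, but gives no response rate for either. The synopsis also states "Number of Subjects to be Enrolled: 115 patients".

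**The concern.** A significance level and a power describe a test of one value against another. Here the sentence on power refers back to a difference, but the sentence before it holds a single rate. The protocol gives no control arm, historical rate, null value, margin or success threshold from which a second rate could be taken. The analysis planned for the CRR is an interval estimate, which has a precision but no power.

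The sample-size justification is therefore incomplete where it stands. A reader cannot check it, cannot tell which hypothesis was meant, and cannot say what observed CRR would count as having shown the difference. If a reference rate were brought in once results were known, the 5% and 90% in the protocol would not describe the resulting comparison.

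**Working it through.** **Inputs from the protocol synopsis.** Expected CRR p1 = 0.73; two-sided significance 5%; power 90%; required size 150 (all from Assumptions); enrolment 115 (number of subjects); one arm (Background). The reference rate p0 is not given.

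**Step 1: try to reproduce 150.** For one proportion against a fixed reference, by the normal approximation,

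n = [(1.960·√(p0(1−p0)) + 1.282·√(p1(1−p1))) / (p1−p0)]².

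With p1 = 0.73, √(0.73 × 0.27) = 0.444, but p0 is needed twice and is missing. The figure cannot be reproduced. Taking p0 = 0.60 purely as an assumption: (1.960 × 0.490 + 1.282 × 0.444) / 0.13 ≈ 1.529 / 0.13 ≈ 11.76, and 11.76² ≈ 138.4, so n = 139. Other assumed references give:

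| Assumed p0 | n for 90% power |
|---|---|
| 0.50 | 46 |
| 0.55 | 74 |
| 0.60 | 139 |
| 0.61 | 162 |
| 0.65 | 354 |

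Solved backwards, this formula returns 150 at p0 of about 0.605 and 115 at about 0.587.

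**Step 2: exact power at the two stated sizes.** Let r be the smallest count with P(X ≥ r | n, p0) ≤ 0.025, the upper half of a two-sided 5% test. Power is P(X ≥ r | n, 0.73).

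| Assumed p0 | n = 115: r, power | n = 150: r, power |
|---|---|---|
| 0.55 | 75, 97.4% | 95, 99.6% |
| 0.60 | 80, 82.6% | 103, 90.0% |
| 0.65 | 86, 37.8% | 110, 50.6% |
| 0.70 | 91, 8.2% | 117, 9.7% |

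**Step 3: the largest reference that keeps 90% power.** By the exact test at n = 115, this is about 58.4%. Above it the cut-off rises to 79 responders and power falls to 87.3%, which is also the exact power at the 58.7% found in Step 1. At n = 150 the limit is about 60.5%, where the cut-off is 103 and power is 89.96%, or 90% after rounding.

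**Step 4: read it as a two-arm comparison.** To give 90% power, 75 patients per arm (150 in total) would need a comparator CRR of about 47%, and 150 per arm about 55%. Neither a second arm nor such a rate is in the protocol, so this reading does not recover the missing input.

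**Step 5: what the planned analysis does deliver.** The 95% half-width at 73% is 1.960·√(0.73 × 0.27 / n): 8.1 points at n = 115 and 7.1 points at n = 150.

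**The case against.** The best defence is that estimation is a legitimate phase 2 aim. The objective is to evaluate the CRR, the planned output is a count with an interval, and no go/no-go decision is stated. An interval of ± 7 to 8 points is a useful result. That stands. A reader might infer that the trial cannot reach a conclusion on its primary endpoint, but the protocol does not support this, because an estimate with its interval answers the objective as worded.

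A second defence is that the protocol names the software used, so a reference rate may have been entered and simply not carried into the text, and a statistical analysis plan not shown here may hold it. That may be so. A reference near 60% would make 150 coherent, so it does not follow that the sponsor's arithmetic is wrong. Nor does anything in the protocol show an intention to choose a benchmark after the data are seen.

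Neither defence rescues the sentence itself. The protocol, not a later document, asserts a required size, a significance level and a power for a difference that it never defines. The general mention of Fisher's exact test does not fill the gap, because that test compares groups and cannot set one arm against a fixed rate.

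**Conclusion.** The point holds as a fault in the stated basis of the sample size. The 5% and 90% belong to no planned analysis, and 150 cannot be derived from what is written. The gap matters: moving the assumed reference from 55% to 70% takes exact power from 97% to 8% at 115 patients and from 99.6% to 10% at 150.

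These figures assume a true CRR of 73%, an exact one-sample test with an upper tail of at most 2.5%, and every patient evaluable. The reference rates are illustrations and must not be attributed to the sponsor. The finding is that the hypothesis is undefined. It does not show that 150 is miscalculated or that estimating the CRR is an unsound aim.

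The disagreement between 115 and 150 is a separate error, and this point stands at either size.

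**What to change.** Choose one of two routes.

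(a) If a reference CRR was set in advance, state the value entered in the sample-size software and its source. Make the primary analysis a one-sample exact binomial test against it, with success declared if the lower limit of the exact (Clopper-Pearson) 95% interval exceeds the reference. That interval agrees with the exact test by construction. Restate the power for the number of patients actually to be enrolled. The reference should come from evidence and not be worked back from the sample size.

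(b) If no reference was set in advance, delete the difference, significance and power wording and justify the size by precision: an expected 73% with a 95% half-width of 8.1 points at 115 patients or 7.1 points at 150.

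Under either route, reconcile 115 with 150 first, since the restated power or precision depends on it. The cost is protocol wording, with no added procedures, and this point by itself calls for no added patients. Under (a) the sponsor commits to a threshold in advance; under (b) it gives up the power claim.

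### The protocol gives two incompatible sample sizes, 115 to be enrolled and 150 required for 90% power, and does not show which is the error

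*Protocol*

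**What the plan says.** The Synopsis header fixes the size of the trial: "Number of Subjects to be Enrolled: 115 patients".

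Under Statistical Plans, Assumptions, the expected result is "We estimate that 73% of patients in the R2 group would achieve CR", followed by "One-hundred and fifty patients will be required to show this difference with 5% significance (two-sided) and 90% power". The sample size is attributed to PASS software. No reference or null CRR is given, and the test is not named.

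The Background describes the design as single-arm ("We plan a phase 2, single-arm trial to evaluate the efficacy and safety of rituximab plus lenalidomide"), and the primary endpoint is fixed in Statistical Plans: "The primary endpoint will be CRR at the end of treatment". Both sample sizes are current text in one synopsis dated 01 Sep 2018.

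**The concern.** A trial has one planned size, and this protocol gives two that differ by 35 patients. Normally a larger enrolment figure and a smaller required figure are linked by an allowance for drop-out. Here the order is reversed: fewer patients are to be enrolled than are said to be required. The protocol mentions no staged design, sample-size re-estimation or separate evaluable population that could explain it.

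The 90% power is the only operating characteristic claimed for the primary endpoint. It is attached to 150, while enrolment is set at 115. As written, nobody can check whether the claim applies to the trial that will be run. In an open, single-arm study, an unclear target also leaves room to defend either number after responses have been seen.

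**Working it through.** **Inputs from the protocol.** Enrolment 115 (Synopsis header). Required size 150, two-sided α = 0.05, power 0.90, expected CRR p1 = 0.73 (Statistical Plans, Assumptions). The reference rate p0 is not stated.

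**Size of the gap.** 150 − 115 = 35 patients, and 35/150 = 23%.

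**Can 150 be reproduced?** Not directly, because p0 is missing. I assume a one-sample test of a proportion with the null variance under the null:

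n = [(1.960·√(p0(1−p0)) + 1.282·√(p1(1−p1))) / (p1 − p0)]², with √(0.73 × 0.27) = 0.444.

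| Assumed p0 | n for 90% power (normal) |
|---|---|
| 0.55 | 74 |
| 0.58 | 105 |
| 0.59 | 120 |
| 0.60 | 139 |
| 0.605 | 150 |
| 0.61 | 162 |

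For p0 = 0.605: [(1.960 × 0.489 + 1.282 × 0.444)/0.125]² = (1.527/0.125)² = 149.2, rounded up to 150. Solving the same formula for n = 115 gives p0 of about 0.587. Either figure can therefore come from an ordinary calculation. They correspond to reference rates less than 2 points apart, and the protocol states neither rate.

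**If 150 is the calculated size, what does 115 deliver?**

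Normal approximation: power = Φ[((p1 − p0)√n − 1.960·√(p0(1−p0))) / √(p1(1−p1))]. At n = 115 and p0 = 0.605 this is Φ[(0.125 × 10.724 − 0.958)/0.444] = Φ(0.861) = 80.5%. With the unrounded p0 of 0.6053 it is 80.3%.

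Exact binomial, upper tail at most 0.025:

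| p0 | n = 150: reject at, power | n = 115: reject at, power |
|---|---|---|
| 0.60 | ≥103, 90.0% | ≥80, 82.6% |
| 0.605 | ≥103, 90.0% | ≥81, 76.8% |

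At 150 the exact power is 89.96% at both reference rates. At 115 the critical count moves by one patient, so power ranges from about 77 to 83%. Using the alternative variance in the normal formula moves the implied p0 to 0.6125 and the power at 115 to 81.0%, inside that range.

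**If 115 is the calculated size.** At p0 = 0.587 the normal formula gives 90% at 115 and about 96% at 150. The exact test at 115 gives 87.3% (reject at ≥79) for p0 = 0.587 and 91.0% (reject at ≥78) for p0 = 0.58.

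**Precision, which needs no p0.** The half-width of the protocol's normal-approximation 95% CI at 73% is 1.96·√(0.73 × 0.27/n): 8.1 points at 115 (64.9% to 81.1%) and 7.1 points at 150 (65.9% to 80.1%).

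**The case against.** The strongest reply is that 150 may simply be a typing error. It is written in words, and *fifty* is an easy slip for *fifteen*. In that case 115 is the calculated size, the 90% power may be intact, and the defect is one wrong word. Nothing in the protocol excludes this. A reader might infer from the two figures that the trial is underpowered, or that 115 fails to deliver the stated power. The documents do not support that inference, because it takes 150 as correct.

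It can also be said that every power figure above rests on a reference rate obtained by working backwards from a disputed sample size, and on a one-sample test that the protocol does not name. The statistical section even uses language about randomised treatment groups, which sits badly with a single-arm trial. This stands: the figures illustrate one branch and are not properties of the design. A two-group reading would not reconcile the numbers either. With 73% against an assumed 47%, a total of 150 gives 91.0% power and a total of 115 gives 82.1%, so the gap has a similar cost.

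Finally, only the Synopsis header sets an enrolment target; the 150 is a statement of statistical need. To say that the site has two accrual stopping points is therefore arguable. The loss of precision, one percentage point of half-width, is also modest for a phase 2 trial. Both remarks are fair, but neither removes the contradiction.

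**Conclusion.** The contradiction is certain: 115 and 150 cannot both be the sample size of this trial, and nothing in the protocol reconciles them. Which figure is the error cannot be determined, because the difference to be shown has no stated reference rate.

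The consequence for power is conditional. If 150 was calculated, 115 patients give roughly 77 to 83% power, assuming a one-sample two-sided 5% test, a true CRR of 73% and an implied reference rate of about 60 to 60.5%. If 115 was calculated, the 90% may hold. Confidence is high for the inconsistency only; a loss of power is not shown. The matter still has to be settled, since it concerns the size of the trial and the only power claim made for its primary endpoint.

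**What to change.** 1. Recover the PASS calculation. State in the Assumptions paragraph the reference CRR and the test it used, and which sample size it produced.
2. Use that one number in the Synopsis header and in the Assumptions paragraph. If the output confirms 115, replace the 150.
3. If the output shows 150 but enrolment stays at 115, replace the 150 and state the power that 115 delivers against the reference rate actually used. The reference should not be one of the back-solved values above: they come from inverting a disputed sample size, and 58.7% does not reach 90% power at 115 under the exact test.
4. With enrolment at 115, add the expected precision: 73% ± 8.1 points.

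The cost is one corrected paragraph and no extra patients. The stated power may become less favourable, but only if 150 proves to be the calculated figure.
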